## Part2

### 1. Title of Proposal:

# **Protective effect of Gum Arabic (*Acacia Senegal*) supplementation on immune responses and inflammatory markers among COVID 19 Patients**

## **Double Randomized two arms clinical trial**

### Introduction:

COVID 19 Coronavirus disease (COVID-19) is caused by SARS-COV2 and represents the causative agent of a potentially fatal disease caused global public concern. The disease spreads rapidly compared to the previous pandemics, which makes it more difficult to contain. Due to this, there is an urgent need for fast diagnosis, preventive and therapeutic measures. Patients infected with COVID-19 showed higher leukocyte numbers, abnormal respiratory findings, and increased levels of plasma pro-inflammatory cytokines. Main mechanism for ARDS (Acute Respiratory Distress Syndrome) is the cytokine storm, uncontrolled systemic inflammatory response resulting from the release of pro-inflammatory cytokines. The cytokine storm will trigger a violent attack by the immune system to the body, cause ARDS and multiple organ failure, and finally death in severe cases. Current investigations, demonstrated that T cell numbers are negatively correlated to serum IL-6, IL-10 and TNF- $\alpha$  concentration, and proposed T cells as potential therapeutic target.

Butyrate, is an epigenetic regulator via its capacity to act as a histone deacetylase (HDAC) inhibitor. This may be directly relevant to the modulation of covid-19 infection. Although data on the biological interactions of covid-19 with human physiology have still to be published, HDAC inhibition is a common regulator of the effects of many viruses, including the influenza virus. The inhibition of HDAC1, as induced by butyrate, decreases influenza-driven pneumonia infections.

Gum Arabic (GA) is a safe dietary fibres approved by FDA and WHO. It is high molecular weight polysaccharide retrieved from *Acacia Senegal* and *Acacia Seyal* trees. GA fermentation produced short chain fatty acids mainly propionate and butyrate. Gum Arabic has anti-inflammatory effect

which has been investigated in various diseases and conditions.

## **Scientific Background:**

### **COVID 19 Pathogenesis:**

COVID 19 Coronavirus disease (COVID-19) is caused by SARS-COV2 and represents the causative agent of a potentially fatal disease that is of great global public health concern(1, 2).

Patients infected with COVID-19 showed higher leukocyte numbers, abnormal respiratory findings, and increased levels of plasma pro-inflammatory cytokines(1-3). Additionally, a value of 16.16 mg/L of blood C-reactive protein was noted which is above the normal range (0–10 mg/L)(2). Patients infected with COVID-19 showed higher leukocyte numbers, abnormal respiratory findings, and increased levels of plasma pro-inflammatory cytokines. Significantly high blood levels of cytokines and chemokines were noted in patients with COVID-19 infection that included IL1- $\beta$ , IL1RA, IL7, IL8, IL9, IL10, basic FGF2, GCSF, GMCSF, IFN $\gamma$ , IP10, MCP1, MIP1 $\alpha$ , MIP1 $\beta$ , PDGFB, TNF $\alpha$ , and VEGFA(1) The latest report shows the number of CD4+ and CD8+ T cells in the peripheral blood of SARS-CoV-2-infected patients significantly is reduced, Similarly, the acute phase response in patients with SARS-CoV is associated with severe decrease of CD4+ T and CD8+ T cells(3). The report in Lancet shows ARDS is the main death cause of COVID-19. Of the 41 SARS-CoV-2-infected patients admitted in the early stages of the outbreak, six died from ARDS(3). Main mechanism for ARDS is the cytokine storm, the deadly uncontrolled systemic inflammatory response resulting from the release of large amounts of pro-inflammatory cytokines (3).The cytokine storm will trigger a violent attack by the immune system to the body, cause ARDS and multiple organ failure, and finally lead to death in severe cases of SARS-CoV-2 infection(1, 2) . IFN-I(IFN- $\alpha$  and IFN- $\beta$ ) has a protective effect on SARS-CoV and MERS-CoV infection, but the IFN-I pathway is inhibited in infected mice(4). n Number of total T cells, CD4+ and CD8+ T cells were dramatically reduced in COVID-19 patients, especially among elderly patients ( $\geq 60$  years of age) and in patients requiring Intensive Care Unit (ICU)(3). Statistical analysis demonstrated that T cell numbers are negatively correlated to serum IL-6, IL-10 and TNF- $\alpha$  concentration, potential therapeutic targets preventing cytokine storm.

### **Gum Arabic mechanism of action:**

Gum Arabic fermentation increased the level of serum butyrate. Butyrate, including in its nutraceutical form, sodium butyrate, is an epigenetic regulator via its capacity to act as a histone deacetylase (HDAC) inhibitor. This may be directly relevant to the modulation of covid-19 infection(5). Although data on the biological interactions of covid-19 with human physiology have still to be published, HDAC inhibition is a common regulator of the effects of many viruses, including the influenza virus. The inhibition of HDAC1, as induced by butyrate, decreases influenza-driven pneumonia infections(5)

Gum Arabic (GA) is a safe dietary fibres approved by FDA and WHO(6). It is high molecular

weight non-starch polysaccharide retrieved from Achaia Senegal and Achaia Seyal trees(6, 7). GA is mainly fermented by colonic bacteria instead of been digested among humans(8) and animals (6, 7). GA fermentation produced short chain fatty acids mainly propionate and butyrate (6-8). The latter discovered as physiological modifier for different body function like modulation of cell proliferation, apoptosis, regulation of angiogenesis and inflammation(9). Gum Arabic anti-inflammatory effect has been investigated in various diseases and conditions (10-12). GA exerted local anti-inflammatory effects by modifying nuclear factor- $\kappa$ B (NF- $\kappa$ B) on the small intestine(13).

#### **Gum Arabic as anti-inflammatory agent:**

Gum Arabic anti-inflammatory effect has been investigated in clinical trials (10,12). An anti-inflammatory effect of GA was demonstrated via the application of GA in drinking water given to rats with diabetes mellitus by a decrease of TNF $\alpha$  and IL-1 $\beta$  and increase of IL-10 (14).

Interestingly, Bovo et al. investigated the effect of GA on the complement system, as arabinogalactans are reported to be complement system modulators. The authors showed a pro-inflammatory activity of GA by activation of the classical and alternative pathways of the complement system (15). GA exerted local anti-inflammatory effects by modifying nuclear factor- $\kappa$ B (NF- $\kappa$ B) on the small intestine (12). In addition, a reduction of oxidative stress was shown after GA supplementation of drinking water in the liver tissue of rats with type I diabetes (16) and oral GA supplementation in humans suffering from sickle cell anemia (17). GA significantly increased oxidative burst/ROS production of bovine and human granulocytes in a dose-dependent manner (18,19). Similarly, arabinogalactan–protein (AGP) of GA may have pro-inflammatory properties on certain parts of the immune system(18, 20).

From all the above the main pathogenesis of COVID 19 is due to inflammatory process and cytokine storm. Gum Arabic is a prebiotic dietary fibers with proven anti-inflammatory properties and immunomodulatory agent. Nowadays, most of research have carried out on corona-virus are in the primary stages and the exact mechanisms remains unknown, infection spread and deaths are increasing in daily bases, the urge for vaccine and protective elements against the immunological response of the body against the virus is needed.

#### **Justification:**

A novel corona virus from Wuhan in central China, named 2019- nCoV, has recently caused an epidemic of pneumonia in humans and posed a huge threat to global public health. To the Date according to national ECDPC -nCoV has led to more than 2744744 cases including 195387 deaths. Which put heath system word wide in great challenge because no licensed vaccine and specific treatment. Identification of natural products with direct antimicrobial effects or also immunomodulatory effects to boost the innate immune defense is a promising strategy to identify and characterize new treatment or prevention strategies. GA is a well-known traditional herbal medication from Acacia Senegal. Gum Arabic is prebiotic agent, with immune modulator properties. Enhancing natural immunity and ameliorate the cytokines storm, will be of great

benefits for COVID 19 patients to overcome the disease.

### 3. Objectives

#### **General objective:**

Explore the role of Gum Arabic as immune modulator among COVID 19 Sudanese patients.

#### **Specific objectives:**

- 1- To understand the immune response of disease progression and physiological pathway in patients consuming Gum Arabic (Acacia Senegal) for one month.
- 2- To study the innate and acquired mechanisms of defense against the coronavirus (cytokine and antibody responses) in placebo and experimental groups in each.
- 3- To assess clinical progression of the disease in group treated with Gum Arabic (Acacia Senegal)
- 4- Measure the level of anti-inflammatory marker (CRP & TNF $\alpha$ , IL6, IL10, IF $\gamma$ ) before and after GA ingestion

### 4. Methodology

- Study Plan: (Phases, Activities)

Phase III clinical trial

**Method:**

**Study design:** Double blind, randomized placebo controlled clinical trial Phase III.

The study will be conducted on patients with COVID 19 infection for 4 weeks.

**Study setting:** The study will be conducted in Khartoum Isolation centers and Soba hospital Khartoum State Sudan

**Sample size:** All Patients who presented to Gabra and Soba hospital and confirmed with COVID 19 during the study period will be included after satisfying the inclusion criteria

**Study population:** (inclusion and exclusion criteria)

**(Inclusion criteria: )**

1-COVID 19 infected as proved by real time PCR. (Newly diagnosed)

2-Age 8-90 years

3-Both gender

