**Exclusion criteria:**

1-Intubated patients on parental treatment

2- Pregnancy

3- Gum Arabic allergy

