**Randomization and blinding:**

The subjects, after stratification by age and sex, will randomly assigned to receive coded and indistinguishable Gum Arabic or placebo. Randomization will be conducted by using a sequence of computer-generated random numbers by independent individual.

Each participating center will be assigned a special code generated by the computer. The

randomization will be kept by the PI and a research assistant. The assessor for clinical outcomes would be blinded to the randomization status. The research staffs who perform the intervention would not know the assessment results. After the eligibility assessment by viral screening, laboratory and clinical assessments would be conducted at the baseline (after completion of informed consent), at first, second and 4th week

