**Gum Arabic administration:**

GA in powder form, it is a 100% natural extract powder produced mechanically from the wildy grown Acacia Senegal tree with a particle size less than 210 µm. The daily dose is 45 gram per day. It will be given in one sachet to be consumed in the early morning dissolved in 200 ml of water. The GA will be provided to the participants weekly for four weeks (7 sachets for each visit). Standardized questionnaire and check list will be used to collect data about patients' physical examination, weight, height, severity of the symptoms and any side effects. Gum Arabic will be purchased from nature gum company, Khartoum Sudan.

Placebo will be pectin one gram per day. It will be given in one sachet to be consumed in the early morning dissolved in 200 ml of water for 4 weeks.

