**Investigations:**

The procedures for screening will be performed within one week before dosing, except where otherwise stated, and included the following:

- 1- Medical history,
- 2- Physical examination, including weight, height and vital signs.

3- The following routine laboratory tests: (A) CBC (B) serum chemistry

including renal function tests (RFT) and Liver function test (LFT)

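### Entry runs from the PCR diagnosis and follow-up from baseline or assignment, with no symptom-onset date named, which costs some precision (mainly at weeks 1 and 2) and leaves the within-group test open to the mix of illness days

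*Protocol*

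**What the plan says.** - **Entry** (Protocol, Inclusion criteria): "1-COVID 19 infected as proved by real time PCR. (Newly diagnosed". No number of days since the test or since first symptoms is set. The only exclusion tied to disease stage is "1-Intubated patients on parental treatment" (Exclusion criteria).
- **Screening** (Investigations): "The procedures for screening will be performed within one week before dosing". It includes a medical history whose items are not listed.
- **Strata** (Randomization and blinding): "The subjects, after stratification by age and sex, will randomly assigned".
- **Assessment clock** (same section): "laboratory and clinical assessments would be conducted at the baseline (after completion of informed consent), at first, second and 4th week". The primary outcome is change from baseline over up to 4 weeks, and the discharge outcome runs from assignment.
- **Symptom data** (Gum Arabic administration): a questionnaire and checklist cover "severity of the symptoms and any side effects". No onset date is named.
- **Objective 1** (Specific objectives): "To understand the immune response of disease progression and physiological pathway", in patients taking Gum Arabic for one month.
- **Analysis** (section 5): a paired t test of baseline against post-treatment values. No other test and no covariate is named.

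**The concern.** A recent diagnosis limits the time since a test, not the time since the illness began. A patient tested on illness day 2 and another tested on day 16 are both eligible, and both count as week 0. If immune markers rise and then fall during the illness, the same baseline IL6 or CD4 value can be on the way up in one patient and on the way down in the other. Their expected changes a week later then have opposite signs, and adjusting for the baseline value alone cannot separate them.

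Three things could be at stake:

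- precision of the between-arm comparison of marker changes and of time to discharge;
- the meaning of the within-group change that section 5 tests;
- how directly curves by trial week describe the course of the disease, which is part of objective 1.

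**Working it through.** **Is onset used anywhere?** The entry criteria, exclusions, strata, listed investigations, outcomes and analysis were read for it. Entry runs from the PCR test, assessments from baseline and discharge from assignment. Onset date appears in none of these places.

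**The plan's own figure.** There is none to reproduce. The protocol gives no sample size, effect size, SD or marker course, so everything below is illustration under stated assumptions.

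**Idealised simulation** (200,000 patients in each of 18 scenarios).

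Log marker = patient effect + amplitude × exp(−(illness day − 10)² / (2 × 5²)) + noise

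- patient effect: SD 0.5
- amplitude: mean ln 3, ln 5 or ln 10, SD 0.5
- noise: SD 0.4 or 0.6
- illness day at entry: uniform over days 1-7, 1-14 or 1-20

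Gain = 1 − (residual variance with baseline value and a cubic in days since onset) / (residual variance with baseline value only), at 7, 14 and 28 days after baseline. The middle case is days 1-14, 5-fold peak, noise SD 0.6.

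**Less ideal simulation.** Same grid, with three further assumptions: peak day varies between patients (SD 3 days), onset is recalled with error (SD 2 days), and 20% of patients have no symptoms and form their own category.

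| Gain from adding days since onset | Week 1 | Week 2 | Week 4 |
|---|---|---|---|
| Idealised, range | 5-72% | 9-49% | 1-14% |
| Idealised, middle case | 41% | 22% | 3% |
| Less ideal, range | 0.6-33% | 1.6-15% | 0.2-2% |
| Less ideal, middle case | 14% | 8% | under 1% |
| Less ideal, entry on days 1-7 | about 3% or less | about 3% or less | about 3% or less |

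**What this means in patients.** If days since onset explains a share R² of the variance, ignoring it multiplies the required number by 1/(1 − R²).

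- Week 4, middle case, R² = 0.03: 1/0.97 = 1.03.
- Week 1, middle case, R² = 0.14 to 0.41: 1/0.86 = 1.16 to 1/0.59 = 1.69.
- Week 2, middle case, R² = 0.08 to 0.22: 1/0.92 = 1.09 to 1/0.78 = 1.28.

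For scale, assume a standardised effect of 0.5, two-sided 5% level, 80% power and equal arms, which needs 63 per arm. With R² = 0.03 ignored, this becomes 63/0.97 = 64.9, so 65. With R² = 0.20 ignored, it becomes 63/0.80 = 78.75, so 79.

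**The paired t test.** Suppose a proportion p of patients would rise by 0.5 SD and the rest fall by 0.5 SD without any treatment effect. The mean change is 0.5p − 0.5(1 − p).

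- p = 0.5: mean change 0. The SD of change rises by the factor √(1 + 0.5 × 0.5) = 1.12.
- p = 0.2: mean change 0.1 − 0.4 = −0.3 SD.

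So in a within-group test the mix of illness days moves the estimate itself, not only its standard error.

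**The case against.** The strongest reply is that this is a refinement, not an error. Much of it stands.

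- **No marker course in the documents.** A reader might infer from the background that COVID-19 markers rise and fall by illness day. The text does not say so. The sentence "the acute phase response in patients with SARS-CoV is associated with severe decrease of CD4+ T and CD8+ T cells" concerns SARS-CoV, offered as a comparison, and states an association. For COVID-19 the background links low T-cell counts to age and need for intensive care. The rise and fall is an assumption.
- **The primary time point gains little.** Even the idealised case gives only 1-14% at week 4. The larger gains belong to weeks 1 and 2 and shrink markedly once peak day and onset date are allowed to be imprecise. No figure was worked out for time to discharge.
- **No bias between arms.** A reader might infer that mixed illness days bias the comparison. They do not: randomisation balances illness day on average, and chance imbalance is covered by the standard error.
- **Objective 1 can still be read.** Weeks since baseline is a legitimate clock for one month of supplementation. Curves by illness day would add to it; their absence does not defeat the objective.
- **Covariates usually belong in the SAP, which is not shown.** This is right for the model term. But an SAP can adjust only for a date that was collected. The items of the history and questionnaire are not shown, so the onset date may be recorded; the protocol simply does not name it.
- **The covariate needs a between-arm model.** Section 5 names only a within-group test, so the precision gain arises only if the arms are compared in a model.

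**Conclusion.** The point holds as a minor one, an improvement the sponsor could make. The protocol names no onset date and uses none in entry, strata, outcomes or analysis. The loss in a between-arm analysis is one of precision: about 0-14% of residual variance at the week-4 primary time point, with a middle case of 1-3%. The middle case is about 14-41% at week 1 and 8-22% at week 2. These figures depend on an assumed rise and fall around illness day 10 and on the spread of illness days at entry. Separately, the paired t test in section 5 measures the natural course together with any treatment effect, and the mean of that course depends on the mix of illness days at entry.

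**What to change.** 1. Add the date of first symptom, with a separate category for patients without symptoms, to the medical history already listed under Investigations.
2. Include days since onset, as a smooth term or in bands such as up to 5, 6-10 and over 10 days, together with the baseline value in a between-arm model of marker changes at weeks 1, 2 and 4. Include days since onset in the between-arm model of time to discharge as well.
3. For objective 1, show marker courses against illness day as a supplement to the display by trial week.

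Eligibility can stay as it is. The cost is one recalled date per patient and one model term, with no extra visit or sample. The downsides are recall error, which reduces the gain, and the need to handle patients without symptoms separately. The date is best collected at entry, since it is harder to recover later.

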**Exclusion criteria:**

1-Intubated patients on parental treatment

2- Pregnancy

3- Gum Arabic allergy

**Randomization and blinding:**

The subjects, after stratification by age and sex, will randomly assigned to receive coded and indistinguishable Gum Arabic or placebo. Randomization will be conducted by using a sequence of computer-generated random numbers by independent individual.

Each participating center will be assigned a special code generated by the computer. The

randomization will be kept by the PI and a research assistant. The assessor for clinical outcomes would be blinded to the randomization status. The research staffs who perform the intervention would not know the assessment results. After the eligibility assessment by viral screening, laboratory and clinical assessments would be conducted at the baseline (after completion of informed consent), at first, second and 4th week

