## 5. Data analysis (Methods used for Data analysis)

**Data will be collected and coded and entered in excel sheet.**

SPSS .24 and Graph prism will be used. Paired *t* test will be used to determine statistical significance between baseline and post treatment results. *P* equal to or less than .05 will consider statistically significant. Data will be presented as means ( $\pm$ SD).

- **References:**

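### Randomisation is stratified by age and sex, but the only stated analysis is a within-patient paired t test that uses neither the arms, the strata nor the recorded symptom severity

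*Protocol*

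**What the plan says.** - **Allocation** (Protocol, Randomization and blinding): "The subjects, after stratification by age and sex, will randomly assigned to receive coded and indistinguishable Gum Arabic or placebo". No age cut-points are given.
- **Centre** (same section): "Each participating center will be assigned a special code generated by the computer". Study setting names more than one site: "The study will be conducted in Khartoum Isolation centers and Soba hospital Khartoum State Sudan".
- **Analysis** (Protocol, section 5, Data analysis): a paired t test "will be used to determine statistical significance between baseline and post treatment results", judged at the 0.05 level. No other inferential method appears.
- **Background** (COVID 19 Pathogenesis): T-cell numbers were reduced "especially among elderly patients", aged 60 or over, and also "in patients requiring Intensive Care Unit (ICU". The same paragraph reports that T-cell numbers correlate negatively with IL-6, IL-10 and TNF-alpha. The specific objectives list those cytokines as study markers, and the laboratory tests include CD4 counts.
- **Severity data** (Gum Arabic administration): the questionnaire and check list record "severity of the symptoms and any side effects". The exclusion criteria remove only intubated patients on grounds of severity, so a wide range of illness can enter.

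**The concern.** Stratifying an allocation declares in advance that the factors matter to the outcome. An analysis that cannot use those factors throws away the precision that the stratification was meant to secure. Here the mismatch goes further, because the one test named looks at change within patients and does not contrast gum arabic with placebo.

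The protocol's own background gives a reason to use severity as well as age. Both appear in the same statement about T-cell loss, and severity is already on the data collection form. At stake are the precision of the treatment comparison and its exposure to a chance difference in severity between arms. Both matter most if the trial is small, and the protocol fixes no number of patients.

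**Working it through.** The protocol gives no sample size, power, effect size, standard deviation or allocation ratio, so there is no figure of its own to reproduce. Steps 2 to 4 use assumed inputs, marked as such, with 1:1 allocation.

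**Step 1. Set the sections side by side.** Allocation uses arm, age and sex. The stated test uses only two values per patient, before and after. Arm, age, sex, centre and severity are all absent from it.

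**Step 2. What the stated test responds to.** Let d be the mean natural change divided by the SD of change, and n the patients in one arm. With no treatment effect, the chance of a significant result within that arm is about Φ(d√n − 1.96) + Φ(−d√n − 1.96). For d = 0.3 (assumed):

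- n = 25: d√n = 1.50, result 0.323
- n = 50: d√n = 2.12, result 0.564
- n = 100: d√n = 3.00, result 0.851

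A significant paired test can therefore reflect recovery alone. Covariate adjustment has a purpose only once the arms are compared.

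**Step 3. Gain from adjusting a between-arm comparison.** If the covariates jointly explain a share R² of the residual variance (assumed), the variance of the treatment estimate is multiplied by 1 − R². The equivalent gain in patients is 1/(1 − R²) − 1. For scale, the number per arm to detect 0.5 SD with 80% power at two-sided 0.05 (all assumed) is 2(1.96 + 0.84)²(1 − R²)/0.5², or about 62.8(1 − R²), rounded up.

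| R² | Equivalent extra patients | n per arm |
|---|---|---|
| 0 (unadjusted) | – | 63 |
| 0.10 | 11% | 57 |
| 0.20 | 25% | 51 |
| 0.30 | 43% | 44 |

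**Step 4. Chance imbalance in severity.** Suppose 30% of patients are severe (assumed) and severity plays no part in allocation. The SD of the difference in proportions between arms is √(2 × 0.3 × 0.7/n), with n per arm. The last column is the chance of a difference of 10 percentage points or more in either direction.

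| n per arm | SD of difference | Chance of ≥ 10 points |
|---|---|---|
| 25 | 0.130 | 0.440 |
| 50 | 0.092 | 0.275 |
| 100 | 0.065 | 0.123 |

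At 60 per arm the SD is 0.084, so the 95% range is about ±1.96 × 0.084, or ±16 points.

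**The case against.** **Pairing already removes stable differences.** Subtracting baseline takes out much of what age, sex and severity contribute to the level of a marker, and the background speaks of levels while the primary outcome is a change. This is partly right: nothing in the document shows how far severity predicts change, so R² could be small. It does not rescue the stated test, which still leaves out the arms. With the baseline value as a covariate, analysis of covariance gives the same treatment effect whether the post-treatment value or the change is modelled, so it fits the stated outcome.

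**Covariate lists belong in a statistical analysis plan, which is not shown.** This stands as far as a missing list goes, and equally for block sizes. But the protocol does not leave the method open: it names a test that has no place for the strata.

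**Stronger readings that a reader might infer, and that the documents do not support:**

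- *The background names centre as driving the immune markers.* It names older age and need for intensive care, and says nothing of centre.
- *Centre is unbalanced.* The computer-generated centre code may mean a separate list per centre; the text does not settle it.
- *The standard errors are too wide.* That would describe an unadjusted between-arm test after allocation that truly balanced the strata. The plan states no such test.
- *The stratification balances nothing.* This rests only on blocks not being mentioned, which is silence. It also conflicts with the previous reading, which needs balanced strata.
- *Severity is the strongest prognostic factor, so the stratification factors must change.* The document does not rank the factors. Adding severity as a stratum, or swapping it for sex, is a design trade-off and does not correct an error.

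**Conclusion.** The point holds as a mismatch within the protocol: a stratified two-arm allocation, followed by a test that uses neither the arms nor the strata and leaves recorded severity idle. The absence of a between-arm comparison is the more basic defect; the covariates determine how good its replacement will be.

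The gain from adjustment is about 11% to 43% in equivalent patients if R² lies between 0.10 and 0.30, relative to an unadjusted comparison of arms. It also guards against severity imbalances that, with the assumed 30% severe, would reach 10 points in roughly one trial in eight at 100 per arm and in more than two of five at 25 per arm. The R², the arm sizes and the severity mix are assumptions; none is in the protocol.

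A reader might infer that leaving out the covariates biases the comparison or inflates type I error. It does not: randomisation protects against systematic imbalance, and the loss is in precision and in exposure to chance imbalance. The false signal in step 2 of the working comes from not comparing arms and is not caused by omitting the strata.

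**What to change.** In section 5, replace the paired t test as the primary analysis with an analysis of covariance of the post-treatment marker:

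- arm as the effect of interest, reported as an adjusted difference with its confidence interval;
- covariates: the baseline value of the marker, age group as used in the randomisation list, sex, and symptom severity as recorded at baseline;
- centre as a further covariate if allocation is by centre, with one sentence in the randomisation section saying what the centre code does.

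Paired summaries of change within each arm can stay as description. The stratification factors need not change.

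The cost is wording and a few degrees of freedom: one each for the baseline value and sex, and one for each level beyond the first of age group, severity and (if used) centre. No new data are needed. If enrolment has begun the change can still be made, provided it is fixed before unblinding.

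### The protocol claims a double blind with indistinguishable products, but specifies a 45 g active sachet against a placebo sachet whose only named content is 1 g of pectin

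*Protocol*

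**What the plan says.** The Method section of the protocol describes the design as "Double blind, randomized placebo controlled clinical trial Phase III". Under Randomization and blinding, patients are "randomly assigned to receive coded and indistinguishable Gum Arabic or placebo".

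The Gum Arabic administration section defines the two products:

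- **Active:** "it is a 100% natural extract powder produced mechanically", with a stated maximum particle size and a named supplier. "The daily dose is 45 gram per day. It will be given in one sachet", taken in 200 ml of water.
- **Placebo:** "Placebo will be pectin one gram per day. It will be given in one sachet to be consumed in the early morning", also in 200 ml of water, for four weeks.

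Two further safeguards appear under Randomization and blinding: "The assessor for clinical outcomes would be blinded to the randomization status", and "The research staffs who perform the intervention would not know the assessment results". The same section says "laboratory and clinical assessments would be conducted at the baseline" and at later visits, so it separates laboratory from clinical assessments. The blind it states is for the clinical assessor.

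**The concern.** A placebo can support a double blind only if the people who take it and hand it out cannot recognise it. Here the product descriptions point the other way: the sachet count and water volume are the same, but the stated contents are far apart in quantity. A code on the label does not hide a large difference in weight and powder volume.

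The outcomes are not equally exposed:

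- **Symptoms and side effects** are collected by questionnaire and are the most exposed, although they are not named as primary or secondary outcomes.
- **Discharge** is a secondary outcome. The protocol does not say who decides it or whether that person knows the arm.
- **Clinical improvement** is a secondary outcome with no stated method of measurement. Even with a blinded assessor, it can be affected by what patients report and by care from staff who recognise the product.
- **The immune response score**, the primary outcome, is exposed only indirectly, since the listed methods are laboratory assays.

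A report of a double-blind trial with indistinguishable products would therefore rest on matching that the protocol does not describe.

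**Working it through.** The plan gives no figure of its own to reproduce. The check sets the blinding claim against the product specification.

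**Inputs, all from the Gum Arabic administration section**

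- Active dose: 45 g per day, one sachet, 200 ml of water
- Placebo dose: 1 g of pectin per day, one sachet, 200 ml of water
- Active supply: 7 sachets per weekly visit for four weeks

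**Arithmetic**

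| Quantity | Formula | Gum Arabic | Placebo as named |
|---|---|---|---|
| Stated content per sachet | dose | 45 g | 1 g |
| Per 100 ml of water added | dose / 200 × 100 | 22.5 g | 0.5 g |
| Weekly supply | 7 × dose | 315 g | 7 g |
| Four-week total | 28 × dose | 1260 g | 28 g |

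The placebo weekly figure assumes that placebo is also handed out seven sachets at a time, which the protocol states only for Gum Arabic.

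- Mass ratio: 45 / 1 = 45
- Filler needed to equalise sachet weight: 45 − 1 = 44 g
- Filler as a share of a matched placebo sachet: 44 / 45 = 97.8%

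**Reading the text**

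The protocol text names no filler, bulking agent, fill weight or matching of the dissolved drink. The only statement of matching is the word indistinguishable, which asserts a result without giving the means.

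The other two safeguards do not fill the gap. Blinding the clinical assessor does not blind the patient. Keeping the intervention staff from the assessment results does not keep them from knowing the allocation. Blinding of patients and dispensing staff therefore depends entirely on the products being alike, and blinding of the laboratory is not stated.

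**The case against.** The strongest reply is that 1 g is a pectin dose and not a fill weight. On that reading the placebo sachet is bulked to match, the blinding section states the required result, and the administration section merely leaves out how it is reached. That reading cannot be excluded. It does require about 44 g of unmentioned material, nearly the whole sachet, in a section that describes the active powder down to particle size and supplier. If such a filler exists, it should be named in any case, because patients would swallow it daily for four weeks. This is product specification, so it is not something to leave to a statistical analysis plan.

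Other objections stand in part:

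- Each patient sees only one product, and the protocol does not describe packaging, taste or texture. The inference is firmer for staff who handle both products than for patients, for whom it is plausible but not proved by mass alone.
- The missing statement on laboratory blinding is a separate omission. It matters here only because coded samples would protect the primary outcome if the double-blind claim has to be dropped.
- Removing the double-blind label would be too strong if matching has been arranged and simply not written down. Stating the placebo's composition would then be enough.

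**Conclusion.** The point holds: the blinding claim is wrong as written. Followed literally, the specification yields products that differ 45-fold in stated mass, and these are not indistinguishable. This should be fixed but is not fatal, because the clinical assessor is stated to be blinded and the primary outcome appears to be measured in the laboratory.

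The conclusion assumes that the administration section gives the full content of the placebo sachet. If the sachet in fact holds about 44 g of a suitable filler, the fault reduces to an undocumented specification. No size of bias is claimed, since the document gives nothing from which to derive one.

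**What to change.** **Preferred.** In the Gum Arabic administration section, specify a placebo sachet matched to the active one in fill weight, appearance and dissolved drink, and name the filler. If this has already been arranged, the cost is a few lines of text. If not, the protocol does not allow a judgement of feasibility or manufacturing cost.

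**If matching is not feasible:**

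1. Remove the double-blind label from the Method section and the claim of indistinguishable products from Randomization and blinding, and describe the trial as assessor-blinded.
2. Send laboratory samples under code so that the primary outcome is read without knowledge of the arm.
3. State that patient-reported and discharge outcomes will be interpreted as open to bias.
4. Confirm that neither the principal investigator nor the research assistant, who hold the randomization, acts as outcome assessor. Otherwise the assessor-blinded label would not hold either.

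This second route costs wording changes and coded labels. Its drawback is a weaker blinding claim: it corrects the description but does not restore the patient blind.
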